## Abstract

**Background:**

Youth who are experiencing homelessness face a higher risk of HIV infection compared to their housed peers, and suicide and overdose remain the leading causes of death among homeless youth. Just-in-Time Adaptive Interventions (JITAIs) are gaining momentum for HIV prevention and substance use research. Yet, most interventions for homeless youth have not addressed modifiable real-time factors.

**Objective:**

This paper describes the development and implementation of a randomized attention-controlled trial to assess the efficacy of motivating youth to reduce infections, disconnections, and emotional dysregulation (MY-RIDE), a JITAI to improve HIV prevention and substance use in homeless youth.

**Methods:**

This study will enroll 320 homeless youth aged 18-25 years. The intervention was co-designed with homeless youth using the Information-Motivation-Behavioral Skills Model and consists of an individual nurse-led session about HIV prevention and 3 months of a JITAI with personalized messaging delivered by phone in real time in response to one’s current level of risk. Participants also had access to an on-demand nurse helpline through the app.

**Results:**

Institutional review board approval was obtained in the summer of 2024. Recruitment began in the fall of 2024 at shelters, drop-in centers, and other organizations that serve homeless youth. Participants complete a baseline survey and HIV/sexually transmitted infection (STI) testing and are provided with a smartphone with the intervention app. Follow-up surveys and HIV/STI testing are conducted at immediate, 3-, 6-, and 12-month time points post intervention to assess uptake of HIV prevention strategies and substance use reduction. A total of 192 are enrolled to date.

**Conclusions:**

The results of this study will determine whether MY-RIDE increases HIV prevention strategies and decreases substance use when compared to homeless youth in the attention control group. We will also evaluate if MY-RIDE impacts protective factors such as willingness to take pre-exposure prophylaxis medication and use of mental health and substance use services, and antecedents of risk such as stress, substance use urge, and substance use.

**Trial Registration:**

Clinicaltrials.gov NCT06074354; https://clinicaltrials.gov/study/NCT06074354

**International Registered Report Identifier (IRRID):**

DERR1-10.2196/78006

## Introduction

There are an estimated 2.4 million people aged 18 to 25 years who experience homelessness in the United States [1]. The highest HIV risk groups—young men who have sex with men, youth of color, heterosexual Black young women, young adults who inject drugs, youth who engage in trade sex or are sexually exploited, and transgender young women who have sex with men all disproportionately experience homelessness [1,2]. While surviving the dangers of the streets and meeting basic needs, youth experiencing homelessness face enormous difficulties in maintaining their health and well-being [3,4]. Questions remain related to how to best address the persistent HIV disparities among homeless youth. Interventions that address substance use, mental health, and housing while also addressing multiple nonmedical drivers of health that marginalize homeless youth are critically needed [5].

Homeless youth are 6-12 times more likely to become HIV positive than their housed peers [6], with prevalence rates as high as 16% [7]. Yet, homeless youth lack adequate access to HIV prevention, including highly effective pre- and postexposure prophylaxis medications (ie, pre-exposure prophylaxis medication [PrEP] and postexposure prophylaxis medication [nPEP]) [8]. Despite the high proportion of homeless youth found to be eligible for PrEP (84%) in 1 large study, only 29% knew what PrEP was, and very few (14%) reported that they were actively trying to prevent HIV [9].

Substance use and stress increase the risk for HIV [10,11]. High stress predicts condomless sex, inconsistent condom use, more sexual partners, and substance use [12-18], with substance use rates among homeless youth being twice that of housed youth [3,19]. Nearly one-third of homeless youth also meet the criteria for co-occurring substance use and mental disorder diagnoses [20-22], and homeless youth often fail to recognize when they need treatment [23]. Barriers such as where and how to access services, costs, wait times, discrimination, and stigma associated with being homeless, having a mental illness, or using substances perpetuate chronic undertreatment [24-27]. The most common barriers to accessing care include lack of transportation, lack of health insurance, and health care costs [28]. Therefore, HIV prevention efforts must simultaneously address substance use and mental health needs and be readily accessible to be effective [29-32].

Homeless youth are disconnected from health care [33], are highly transient, and geographically mobile, making it difficult to engage in traditional brick-and-mortar care models. Only about half of street-dwelling youth and one-third of sheltered youth use health care regularly [34]. Additionally, homeless youth who use substances or have mental health issues experience compounding barriers to accessing mental health care [16] and HIV prevention measures, such as PrEP [35], with only one-third who need care accessing it [24,36]. While homeless youth continue to be underserved and understudied, prevention interventions specifically targeting homeless youth have achieved improvements in substance and alcohol use [37] and sexual health outcomes when addressing substance-using youth [38]. Interventions that address substance use, mental health, and housing while also addressing multiple nonmedical drivers of health that marginalize homeless youth are critically needed [5].

Ecological momentary assessments’ (EMAs) methodologies are also gaining momentum for HIV prevention and treatment research [39]. Using real-time, personalized motivational and prevention messages may provide more timely delivery of interventions. Yet, few HIV prevention mHealth (mobile health) interventions for homeless youth have been developed or rigorously tested [40]. Building on these mHealth efforts, this intervention uses EMA, Just-in-Time Adaptive Intervention (JITAIs) delivery, and on-demand nurse-led sessions that address substance use and stress management as an innovative, scalable, and accessible way to serve highly transient homeless youth [41].

Motivating youth to reduce infections, disconnections, and emotional dysregulation (MY-RIDE) is an mHealth intervention that uses EMAs to predict imminent risk behaviors and delivers personalized messaging at the time of heightened risk. MY-RIDE addresses HIV risk and its antecedents in real time using messages developed with the Information-Motivation-Behavioral Skills (IMB) model and homeless youth [42]. This nurse-led model offers on-demand education sessions that use motivational interviewing (MI) [43-47] and shared decision-making (SDM) [48,49] approaches to promote behavior change and uptake of coping strategies by facilitating goal setting and increasing motivation and skills (Figure 1). The methods are integrated by using the IMB-informed messages in the app while the nurse delivers the HIV prevention content using MI and SDM strategies. Finally, homeless youth receive personalized messages delivered to their phone that address their current HIV risk factors as well as substance use, stress, and housing needs. Pilot data found that MY-RIDE decreased drug use, sexual urges, and stress among homeless youth [50].

**Figure 1 figure1:**
[figure not shown]
Information, motivation, and behavior guided MY-RIDE. MY-RIDE: motivating youth to reduce infections, disconnections, and emotional dysregulation; nPEP: postexposure prophylaxis medication; PrEP: pre-exposure prophylaxis medication; STI: sexually transmitted infection.

Overall, the current study is guided by the IMB model [42,51]. IMB model posits that 3 primary factors influence behavior changes: information and knowledge about the behavior, in this case HIV risk behaviors; the individual’s motivation to perform the behavior; and the behavioral skills needed to modify the behavior [51]. Applying IMB, we hypothesize that homeless youth will reduce their risk for HIV when they (1) are provided with information on PrEP/nPEP, sexually transmitted infections (STIs), condom use, substance use, stress management, and health care services; (2) are motivated to change behavior by engaging in MI focused on HIV prevention and substance use reduction strategies with a nurse and receiving motivational messages in response to current stress symptoms; and (3) are provided with behavioral skills-building opportunities to reduce and manage stress, surf the urge to use substances or have sex, and increase health care seeking.

This randomized controlled trial will test the effects of MY-RIDE on HIV prevention in Harris County (Houston, Texas), 1 of the 48 Ending the HIV Epidemic counties that accounts for 50% of new HIV cases. The purpose of this trial is to determine whether MY-RIDE decreases substance use and increases HIV prevention strategies (condom use, PrEP uptake, and reduced STIs) compared to an attention control group of homeless youth (N=320; aged 18-25 years) immediately after the intervention and at 3-, 6-, and 12-months postintervention. An additional exploratory aim is to evaluate MY-RIDE effects on willingness to take PrEP, on stress levels, substance use urge, and use of mental health and substance use services when compared with attention control youth.

## Methods

### Study Design and Setting

This study uses a randomized 1:1 attention-controlled design to test the effects of MY-RIDE on substance use and HIV prevention among homeless youth. As there is some potential that EMAs or JITAIs can influence behavior, an attention-control design was chosen over a waitlist-control condition.

### Participants

Participants are being recruited from locations frequented by homeless youth, including the largest homeless youth drop-in centers and the largest homeless youth shelter in Houston, Texas. Both approximate the real-world service organization that would have the capacity to disseminate the intervention if found to be efficacious.

### Inclusion and Exclusion Criteria

The sample will include 320 homeless youth, aged 18-25 years, randomized 1:1 to either the intervention group or the control group. A random sequence generated in R (R Foundation) will be used for the simple randomization to ensure allocation concealment and minimize selection bias. Individuals at high risk for HIV will be included if they (1) have engaged in substance use (alcohol or illicit drugs) in the past 30 days, (2) are aged 18-25 years, (3) speak English, (4) are currently experiencing homelessness, (5) are engaged in sexual activity in the last 6 months or plan to in the next 30 days, and (6) are not planning to move out of the metro area during the 12-month study period. Current substance use is defined as having used any illicit drugs, drugs that are not prescribed, or alcohol in the past 30 days. Homelessness is defined as having slept on the streets, in a place not meant for habitation, a shelter, hotel or motel, or with someone where they cannot stay for more than 30 days (eg, couch surfing). This broader definition of homelessness aligns with the McKinney-Vento Homeless Assistance Act of 1987 and allows us to account for the transiency and instability of housing experienced by homeless youth, and increases the generalizability of this study’s findings. Homeless youth who have low literacy, based on the Rapid Estimate of Adult Literacy in Medicine-Short Form (scores <4), will be excluded due to the need to read independently at a 4th-grade level. We do not anticipate excluding many homeless youth based on this exclusion criterion. Only 1.2% of screened homeless youth from our prior study had low literacy [50].

### Data Collection

Data are being collected at baseline, immediately post intervention, and at 3, 6, and 12 months post intervention using REDCap (Research Electronic Data Capture; Vanderbilt University) on tablets or delivered through a web-based link that is password-protected and sent via text message on the study-issued phone. In-person survey takers are provided a quiet, private room (eg, at the shelter, drop-in center, and library) and most need about 30 minutes for completion of the survey. EMAs are collected 3 times a day for 12 weeks using the Insight App [52] and take about 1 minute to complete. The app is downloaded on this study’s issued smartphone to ensure all participants have functional devices on which to answer the EMAs and be contacted for study visits during the trial. To promote continuous engagement with the Insight app, EMA activity is monitored at 48-hour intervals, and participants are compensated based on percentage completion. Participants who do not complete an EMA in 48 hours are contacted on this study’s issued phone to verify if they are experiencing problems that can be addressed and to encourage EMA completion.

The presence of HIV antibodies, syphilis antibodies, and detection of chlamydia or *Neisseria gonorrhoeae* are being collected at baseline, immediately postintervention, and at 3, 6, and 12 months post intervention. In a private setting, participants complete a finger prick for rapid testing of HIV and syphilis and provide a urine sample for detection of chlamydia and gonorrhea. Tests were not diagnostic; all positive results are referred for confirmatory testing and treatment. Additionally, participants could provide study staff permission to access HIV/STI results from the on-site clinic when tested in the last 2 weeks to reduce testing burden.

Willingness to take PrEP is measured in the follow-up surveys using an item consistent with previous studies [53,61], “How likely would you be to take PrEP if it were available for free?” with response options ranging from “Definitely would not take PrEP” to “Definitely would take PrEP”. The Perceived Stress Scale was also used, consisting of 10 items with response options from 0 (never) to 4 (very often), and can range from 0 to 40. Example item: “How often have you felt that you were unable to control the important things in your life?” Positively worded items are reverse-scored before scores are summed. This scale measures stress-related feelings over the last month, with higher scores indicating greater perceived stress [62,63]. Substance use urge is assessed in the EMAs with the item consistent with pilot study [50], “Right now, I am feeling a strong urge to: (Check all that apply): Steal, drink alcohol, use drugs, have sex, none of the above.” Usage of mental health and substance use services is measured using 2 items in the follow-up surveys: “In the last 3 months, have you used mental health (or substance use) services?” Response options are: “yes,” “no,” and “not sure.”

Measures from the PhenX Toolkit were used whenever possible to enhance data harmonization and data sharing efforts. EMA items measure real-time affect, stress, sexual risk behaviors, and urges (ie, right now), as well as real-time motivation measures. These Likert-type scale items have been successfully used with homeless youth and are based on our prior work and the work by Shiffman et al [50,64-67].

### Intervention Arm

An individual-level intervention design was chosen due to the heterogeneity of homeless youth and variability in real-time risk factors that impact HIV risk and substance use. The intervention, MY-RIDE, has three main components: (1) one nurse-led face-to-face session, (2) three months of EMA with personalized messaging delivered by phone in real time in response to one’s current risk, and (3) access to on-demand health care or PrEP navigation and referrals.

Nurses are ideal for leading the intervention sessions with homeless youth. Not only are nurses continuously ranked as the most trusted profession in the United States, an important consideration when working in a population with high levels of mistrust [68], but nurse-led interventions have the best potential for scalability and have been successful in improving HIV prevention strategies [69] among homeless youth, as they are trained to coordinate care across services through case management [53,70,71]. During the nurse-led face-to-face sessions, the nurse conducts an HIV risk assessment and assesses substance use, stress, and housing needs to guide the discussion about HIV prevention and goal attainment. The standard approach of the Screening, Brief Intervention, and Referral to Treatment tool is used for alcohol and drug use issues [72,73], with the nurse providing either a brief intervention or referral for substance use treatment. Sessions are held in a private setting such as a classroom, office space, library, or another empty room available at the community site.

The session allows for time to discuss HIV prevention strategies and establish a behavioral goal (ie, condom use, PrEP uptake, reduced substance use, sober sex, and reduced sexual partners). MY-RIDE builds on our previous prevention trial that supports the need for frequent, ongoing contact by providing ongoing prevention messages and booster sessions [50]. MY-RIDE participants are referred to local homeless youth-serving agencies to meet the complex, comorbid health or mental health, and social needs of homeless youth. MI and SDM strategies allow the nurse to tailor the discussion to the individual’s needs based on their current risks, chosen goal, and HIV prevention motivation level. The nurses are trained to follow the manualized MY-RIDE intervention session and complete a checklist of core activities to document delivery of Screening, Brief Intervention, and Referral to Treatment, PrEP eligibility, selection of prevention strategy, and referrals made after each intervention participant. Following the session, participants receive a study-issued cell phone with the app installed and general resources programmed for food, housing, and other local services for homeless youth.

The second component consists of 3 EMAs every day for 3 months with personalized messaging after each EMA using the Insight app [52]. Youth receive a targeted prevention message that responds to real-time risk levels at the moment the risk is detected. Real-time risk factors for substance use and HIV risk are based on previous studies and include stress, urge to steal, and urge or indication of sex, drug use, or alcohol use [50,64]. Decision rules for message delivery assign the appropriate message dose and content based on each participant’s current risk factors and relevant tailoring trait variables (eg, gender and sexual orientation) to deliver personalized, time-varying intervention content [65]. Over 900 intervention messages were co-developed with homeless youth and guided by the IMB model, and these were extensively beta tested and used successfully in the pilot [50]. In instances where multiple predictors are equally high, 1 message will be delivered with preference given to the strongest predictors (eg, real-time substance use). The justification for limiting to 1 message per EMA and the hierarchical ordering system based on prediction strength are grounded in the results from Projects Prevail and Smart-T [74,75], which indicated that receiving just 1 targeted message after each EMA reduced response fatigue. When low substance use and HIV risk are detected, a participant will receive more general messages reinforcing, for example, healthy stress management strategies, safety tips, or motivational quotes. Study staff reach out to youth weekly who have not responded to an EMA in 48 hours to assess for and address any challenges they may be experiencing (i.e., needing a phone charger). Additionally, the app automatically populates an interface that provides visual feedback about how one’s current behaviors align with their health goals, which can be accessed on their study-issued password-protected phone during the 3-month intervention period. This serves as an ongoing motivation to align or maintain one’s behavioral goals (Figure 2).

**Figure 2 figure2:**
[figure not shown]
Insight app snapshots of the home screen, EMA item, intervention message, and behavioral feedback visual. EMA: ecological momentary assessment; MY-RIDE: motivating youth to reduce infections, disconnections, and emotional dysregulation; PrEP: pre-exposure prophylaxis medication.

The third component of the intervention includes access to an on-demand nurse helpline. During the face-to-face session, the nurse demonstrates how the participant can reach this study’s nurse using a single “contact nurse” button on the app home page. Participants are advised to use this feature when they have questions about substance use, sexual health, or anything discussed in the face-to-face sessions. A registered nurse who is a part of this study’s team monitors this phone line and is prepared to answer questions and provide resources or local referrals regarding substance use, HIV/STI testing and treatment, PrEP or nPEP, and free condoms. Calls or texts are answered immediately or returned within 24 hours of a business day, and participants are directed to 911 if it is an emergency. Additionally, if a participant indicates that they need an STI test while completing a daily EMA, the nurse will automatically be notified via email and follow up with that participant to offer testing or navigate treatment seeking as needed.

### Control Arm

Participants assigned to the attention control arm will receive a 1-hour general health promotion session from a nurse, research coordinator, or research assistant and be issued a phone that will deploy the EMA on the same schedule as the intervention arm, with general health messages delivered after the EMA. These messages are unrelated to HIV risk, substance use, or its antecedents and address topics such as fruit and vegetable consumption, physical activity, water intake, and sleep hygiene. They will also receive usual care from the clinics, drop-in centers, and shelter recruitment sites. Usual care includes accessing social workers and case managers for immediate housing, food, and clothing needs and assistance in navigating the local continuum of care system to access social services. Specifically, youth are assessed at intake at the drop-in centers and shelters for mental health, substance use, and housing needs. This standard of care does not currently include HIV prevention education, personalized HIV prevention behavioral goal setting, or personalized HIV prevention messaging. Usual care has some evidence of reducing substance use in homeless youth, aged 14-20 years [76]. Attention control youth will also have access to the homeless youth’ resources programmed into the phone. While this is a low-risk study that will increase HIV prevention access and health care use, control youth will be monitored for adverse effects during this study and provided with the contact information for study staff, which will also be preprogrammed into this study’s phone.

### Sample and Power

The sample size (N=320) was determined from considerations of the MY-RIDE intervention effect on substance use (aim 1), STIs, PrEP use, and condom use (aims 2). For substance use, the effect size (odds ratio 0.61, 95% CI 0.39-0.97) was assumed from our previously published results that arose from a generalized linear mixed model framework [50]. Monte Carlo simulations implemented with the SIMR package [77] developed in the R programming language [78] yielded an estimated power of 0.96 for the intervention effect on substance use. Missing data were incorporated in the simulations by using a 50% response rate, from our pilot study, to EMA surveys over the 90-day intervention phase. Power for PrEP use was estimated similarly with a simulation that was based on the observed effect size in our ongoing National Institutes of Health–funded study that is testing a nurse case management intervention. The anticipated strong effect (odds ratio 10.59, 95% CI 2.44-50.90) was countered by the low prevalence of PrEP usage in youth, resulting in power=0.80 for the PrEP use outcome. The effect size (odds ratio 0.34, 95% CI 0.11-1.06) for STI was estimated from the aforementioned study, resulting in estimated power=0.81 for a 1-tailed test (and power=0.71 for a 2-tailed test). Lastly, the effect size (f=0.30) for condom use was estimated from a study involving youth of the same age group [79]. An estimated power=0.96 was determined using G*Power (version 3.1; Heinrich-Heine-Universität Düsseldorf) [80] for the intervention effect on condom use. In summary, estimated power for the primary and secondary outcomes ranged from 0.80 to 0.96 for a sample size of 320, randomized into 2 groups with 160 participants per group. All power calculations assumed α=.05 and included an allowance for 30% attrition, from our pilot study, from baseline to the first follow-up.

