For aim 2, we determine whether MY-RIDE increases HIV prevention strategies—condom use, PrEP uptake, reduced STIs—when compared with an attention control group of homeless youth. Intervention effects on condom use, PrEP uptake, and STI test results will be analyzed with Bayesian mixed effects models [84], following the method described in aim 1 above. We hypothesize that at 3-, 6-, and 12-months follow-up, the use of HIV prevention strategies will be higher in the intervention group than the attention control group. Condom use will be modeled as an ordinal measure (never to every time) and as a binary measure of condom use at the last sexual encounter. PrEP uptake will be modeled as a binary measure that combines the irregular use of PrEP with regular use because both are expected to be found in a small proportion of the data. STIs may be combined if the frequencies of individual STIs (eg, gonorrhea, chlamydia, and syphilis) are low, which will result in an any or none binary measure for STIs. Time will be treated as a discrete variable, and random intercepts will be included per participant. Statistical significance (α=.05) of the fixed effect corresponding to the interaction of time and treatment group will be used for inference of the intervention effect at each follow-up. The primary follow-up of interest is the one immediately following the intervention, while longer-term effects of the intervention will be judged from the follow-ups at 3, 6, and 12 months.

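### The summary power range of 0.80 to 0.96 holds only if the STI outcome is counted at its one-tailed power; on the article's own two-tailed figure the range starts at 0.71

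*Protocol article*

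**What the plan says.** The Sample and Power section of the protocol article gives a power for each of four outcomes at N=320.

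- Substance use (primary): "yielded an estimated power of 0.96 for the intervention effect on substance use".
- PrEP use: "resulting in power=0.80 for the PrEP use outcome".
- STI: the planning effect is an odds ratio of 0.34 with a 95% interval from 0.11 to 1.06, "resulting in estimated power=0.81 for a 1-tailed test (and power=0.71 for a 2-tailed test").
- Condom use: "An estimated power=0.96 was determined using G*Power".

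The paragraph then summarises: "estimated power for the primary and secondary outcomes ranged from 0.80 to 0.96 for a sample size of 320". It closes with "All power calculations assumed α=.05 and included an allowance for 30% attrition", which does not say whether the .05 is one- or two-sided.

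The Instruments section names STIs as a secondary outcome, with condom use and PrEP uptake. For these three outcomes the Data Analysis section says that significance at .05 "of the fixed effect corresponding to the interaction of time and treatment group will be used for inference". It refers back to the aim 1 method, where the threshold is P≤.05. Neither aim specifies a one-tailed test.

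**The concern.** The summary sentence covers every primary and secondary outcome, and its lower bound is the conventional 0.80. Two powers are available for STI, and only the more favourable one fits that bound. The summary does not say that one of its four entries rests on a one-tailed test.

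The analysis section does not support that choice. STI shares one .05 rule with condom use and PrEP uptake, and nothing marks it out for one-tailed testing. A one-tailed test at .05 uses the critical value of a two-sided test at .10. In the favourable direction its false-positive rate is 5%, against 2.5% for a two-sided .05 test.

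A reader who relies on the summary will take a non-significant STI result as coming from a test with at least 80% power. On the two-sided reading it had 71%. Sidedness could also decide the STI conclusion, because the planning effect itself lies between the two thresholds (see the working).

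**Working it through.** **Inputs**, all from Sample and Power: substance use 0.96; PrEP 0.80; condom use 0.96; STI 0.81 one-tailed and 0.71 two-tailed; STI odds ratio 0.34 (95% CI 0.11 to 1.06); N=320; α=.05.

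**Step 1. Reproduce the stated range.** With STI at 0.81, the four powers are 0.96, 0.80, 0.81 and 0.96. The minimum is 0.80 and the maximum 0.96, as stated.

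**Step 2. Use the two-tailed STI figure.** The powers are 0.96, 0.80, 0.71 and 0.96. The minimum is 0.71 and the maximum 0.96. Type II error for STI is 1 − 0.71 = 0.29, against the ceiling of 1 − 0.80 = 0.20 that the summary implies.

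**Step 3. Check that the two STI figures agree** (normal approximation).

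- Standardised effect implied by 0.81 one-tailed: z(0.81) + z(0.95) = 0.878 + 1.645 = 2.523.
- Two-tailed power at that effect: Φ(2.523 − 1.960) = Φ(0.563) = 0.713.
- In reverse, 0.71 two-tailed implies a standardised effect of 2.513, and one-tailed power Φ(2.513 − 1.645) = 0.807.

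Both directions return the printed values. The 0.71 is the same calculation with the other critical value, not a misprint.

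**Step 4. Size of the shortfall in participants.** Two-sided power of 0.80 needs a standardised effect of 1.960 + 0.842 = 2.802. At the same assumed effect and attrition, N scales with the square of the ratio:

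- from 2.523: (2.802 / 2.523)² × 320 ≈ 395;
- from 2.513: (2.802 / 2.513)² × 320 ≈ 398.

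So 0.80 two-sided would take about 395 to 398 randomised, against 320. This only shows the size of the gap and is not a proposal to enlarge the trial.

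**Step 5. Does sidedness matter near the planning effect?**

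- ln(0.34) = −1.079.
- SE ≈ (ln 1.06 − ln 0.11) / 3.92 = (0.058 + 2.207) / 3.92 ≈ 0.578.
- z ≈ −1.079 / 0.578 ≈ −1.87, so two-sided p ≈ 0.06 and one-sided p ≈ 0.03.

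A result like that of the source study would miss a two-sided .05 threshold and pass a one-sided one.

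**What cannot be checked.** The article gives no control-arm STI rate, so neither STI power can be rebuilt from stated inputs. As an assumption only, take 112 per arm (160 less 30%) and control rates from 10% to 25%. Two-tailed power then runs from 0.47 to 0.83. Nothing above depends on this, because 0.81 and 0.71 are both the article's own figures.

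**The case against.** The strongest defence is that nothing is miscalculated or concealed. The 0.71 stands in the same paragraph, correctly labelled, and the stated range follows from the powers if STI is counted one-tailed. The hypotheses are directional, and the article nowhere states that its tests are two-sided. Sidedness is also commonly left to a statistical analysis plan, which is not at hand. STI is one of three secondary outcomes, and the primary outcome is not touched.

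Much of this stands, and it limits what can be claimed.

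- A reader might infer that the article commits to two-sided testing and so contradicts itself outright. It does not: it is silent on sidedness, and the sidedness of the substance use, PrEP and condom use powers is not stated either.
- A reader might infer an arithmetic error. Step 3 rules that out.
- A reader might infer that the authors mean to choose the STI test's sidedness after seeing the data. The article offers no evidence of that, and a plan not shown may already settle it.

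The defence does not rescue the summary sentence. A directional hypothesis is not a one-tailed test. The article states directions for all its outcomes, yet mentions one tail only for STI and only when computing power. Disclosing 0.71 earlier does not make an unqualified range that excludes it correct. Nor is this an omission left to another document: the range is stated here, and it holds only under a test that the analysis section does not specify.

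**Conclusion.** The point holds as a reporting inconsistency in the power summary. On the conventional two-sided reading of α=.05, the article's own figures give 0.71 to 0.96 for the primary and secondary outcomes. The stated lower bound is 0.09 too high, and type II error for STI is 29%.

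The conclusion rests on two things: the article's own 0.71, taken as given, and the reading of an unqualified .05 as two-sided. If a one-tailed STI test were pre-specified and justified, the 0.80 bound would stand, but it would need that label.

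A reader might go further and say that the trial is too small or that its design is compromised. The documents do not support that. One secondary outcome is affected, and this point leaves the allocation, data collection and analysis model as they are.

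**What to change.** In Data Analysis, state that the STI test is two-sided at .05, under the same rule as the other outcomes. In Sample and Power, restate the summary as power from 0.71 to 0.96, with 0.71 attributed to STI. The one-tailed 0.81 may remain in the STI sentence if it is clearly labelled as one-tailed and not used in the range.

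This takes one or two sentences. It changes neither the sample size nor trial conduct. The only cost is a slightly less favourable stated figure for one secondary outcome.
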